### **3.1.3. Treatment Extension Period**

In the absence of progressive disease (PD) and unacceptable toxicity, subjects may receive GSK1363089 treatment on the same dosing schedule for up to a total of 2 years at

the discretion of the investigator and beyond 2 years with the approval of the sponsor while participating in this study. Tumor assessment will continue approximately every 8 weeks while the subject remains on study.

#### **3.1.4. Post-Treatment Period**

Subjects will return to the study site 30 ( $\pm 4$ ) days after the last dose of study drug to complete end-of-treatment assessments. On Days 90 and 180 ( $\pm 15$  days) after the last dose of study drug or until death (if before Day 180), the investigator (or designee) will obtain follow-up information including subsequent cancer treatments, any serious adverse events (SAEs) considered to be possibly or probably related to study drug, death, and date and cause of death.

#### **3.2. Study Sites**

It is anticipated that this study will be conducted at up to 20 clinical sites, mostly in the United States. For the purposes of this protocol, sites using satellite facilities will be counted as one site.

#### **3.3. Treatment Assignment**

It is the responsibility of the investigator to contact GSK (or designee) for a subject number before treating each subject with GSK1363089. GSK (or designee) will have records of the number of subjects treated.

##### **3.3.1. Treatment Groups**

Initially, subjects with a histologic diagnosis of poorly-differentiated, advanced or metastatic gastric carcinoma or adenocarcinoma of the gastroesophageal junction will be eligible for enrollment into Cohort 1 (Intermittent 5&9 dosing), until a total of 30 subjects is determined to be evaluable (see Section 8.1.1 for definition of 'evaluable'). After entry, subjects will be stratified retrospectively into one of the two strata listed below based on the presence of confirmed *c-MET* amplification at 7q31, as defined as at least 3 genomic copies of the *c-MET* gene determined by FISH:

- Stratum A: Subjects with confirmed *c-MET* amplification at 7q31.
- Stratum B: Subjects without confirmed *c-MET* amplification at 7q31.

If fewer than eight of those 30 subjects have amplification of *c-MET*, as defined as  $\geq 3$  genomic copies of the *c-MET* gene (Stratum A), up to 10 additional, evaluable subjects will be enrolled to better characterize the effect of GSK1363089 in this subgroup, with a goal of attaining eight evaluable subjects who have amplification of *c-MET*, as defined as  $\geq 3$  genomic copies of the *c-MET* gene.

After Cohort 1 has completed enrolment, subjects with a histologic diagnosis of advanced or metastatic gastric carcinoma or adenocarcinoma of the gastroesophageal junction or of the distal esophagus will be eligible for enrollment into Cohort 2. This will include subjects with well- and moderately-differentiated tumors, as well as poorly-differentiated tumors. Enrolment into Cohort 2 will continue until a total of 30 subjects are determined to be evaluable. After entry, subjects will be stratified retrospectively into one of the two strata listed below based on the presence of confirmed *c-MET* amplification at 7q31, as defined as at least 3 genomic copies of the *c-MET* gene:

- Stratum A: Subjects with confirmed *c-MET* amplification at 7q31.
- Stratum B: Subjects without confirmed *c-MET* amplification at 7q31.

If fewer than 8 of the evaluable subjects in Cohort 2 have a *c-MET* amplification, as defined as  $\geq 3$  genomic copies of the *c-MET* gene, then up to 10 extra evaluable subjects will be enrolled, in order to have at least 8 *c-MET*-amplified subjects in this Cohort, as defined as  $\geq 3$  genomic copies of the *c-MET* gene.

In addition, as part of Amendment 4.0, subjects in both cohorts will also be stratified according to a more stringent definition of *c-MET* gene amplification (i.e.  $\geq 2$  copies of *c-MET* per copy of chromosome 7). This is because in an analysis of an initial group of Cohort 1 subjects whose tumors had “at least 3 genomic copies of the *c-MET* gene”, a number of them did not have true *c-MET*-gene amplification (i.e.  $\geq 2$  copies of *c-MET* per data from Smolen *et al*, gastric tumor cell lines with true *c-MET*-amplification, consistent with so-called homogeneously staining regions (HSRs), are significantly more sensitive to a specific c-MET tyrosine kinase inhibitor (PHA-665752) than cell lines with no- or low-level-copy number increase, such as those with chromosome 7 aneuploidy (Smolen, 2005).

Therefore, in addition to the definition of *c-MET* amplification used in this protocol up to Amendment 3.0 (i.e. at least 3 genomic copies of the *c-MET* gene), a more stringent

definition will also be used – i.e. those who meet at least one of the following criteria upon FISH analysis:

1. Ratio of the average copy numbers of *c-MET* to *CEP 7*, across at least 60 cells, of at least two;
2. Any cells containing multiple copies of the *c-MET* gene in homogeneously-staining regions (HSRs)

Note - as part of Amendment 4.0, the 2 definitions of *c-MET*-amplification referred to in this section will be written as follows:

- The original definition will be written as “*c-MET* amplification, as defined as  $\geq 3$  copies of the *c-MET* gene”
- The new definition, described above, will be written as “*c-MET* amplification, as defined as  $\geq 2$  copies of the *c-MET* gene per copy of chromosome 7”

In Cohort 2, in addition to requiring at least 8 evaluable subjects to have *c-MET* amplification, as defined as  $\geq 3$  copies of the *c-MET* gene, there will also be a requirement to have at least 4 evaluable subjects who meet the more stringent definition of *c-MET* gene amplification, as defined as  $\geq 2$  copies of the *c-MET* gene per copy of chromosome 7.

In the event that the enrolment of 30 evaluable subjects in Cohort 2 is completed before the target of 4 subjects with *c-MET* amplification (as defined as  $\geq 2$  copies of the *c-MET* gene per copy of chromosome 7) has been reached, then extra *c-MET*-amplified subjects (as defined as  $\geq 2$  copies of the *c-MET* gene per copy of chromosome 7), identified by pre-screening FISH, will be enrolled in the study, until the target is reached.

All subjects will have their diagnosis of gastric cancer confirmed by independent central pathology review (see Section [5.9.4](#)).

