 Prior to Amendment 3.0, only subjects with poorly-differentiated gastric carcinoma or adenocarcinoma of the gastroesophageal junction were included. Amendment 3.0 expanded this, 1) to remove the requirement for poorly-differentiated histology, and 2) to include subjects with distal esophageal carcinoma.

regards to the primary efficacy variable, which is the objective response rate (ORR), defined as the proportion of subjects for whom their best overall response is a confirmed CR or confirmed PR by RECIST:

For each Cohort, if at least 6 of the 30 evaluable subjects respond, this regimen of GSK1363089 will have demonstrated a response rate of 20%. This design is used to test the following hypothesis on the ORR:

$$H_0: P_0 \leq 0.10 \text{ versus } P_a \geq 0.25$$

Assuming a type I error rate (alpha) of 0.10 and a type II error rate (beta) of 0.20, with 30 evaluable subjects and at least 6 observed responses ( $\geq 0.20$ ) subjects, there is a 0.0732 chance of falsely concluding this regimen is preliminarily effective if the true response rate is 0.10. And the chance for falsely rejecting the effect of the regimen is 0.2026 if the true response rate is 0.25. If additional enrollment is required and at least 8 of the 40 ( $\geq 0.20$ ) evaluable subjects respond, then the above two probabilities would be 0.0419 and 0.18196, respectively.

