In the XL880-002 study, GSK1363089 was tolerated when administered for 28 days at doses up to 80 mg/day. Adverse effects include hypertension, fatigue, nausea, vomiting, and asymptomatic changes in laboratory values. The MTD for daily GSK1363089 dosing has been determined to be 80 mg/day. Based on preliminary PK analysis, GSK1363089 accumulates in plasma with repeated daily dosing. Results from pharmacodynamic analyses of plasma and surrogate tissue biomarkers indicate potential biological effects of

GSK1363089 in subjects. Anti-angiogenic pharmacodynamic marker changes have been detected in this clinical trial consistent with effects reported with other anti-angiogenic agents. The clinical observations of decreased tumor size, prolonged stable disease and/or improvement in tumor markers are consistent with the antitumor activity observed in XL880-001. These findings suggest that GSK1363089 dosed daily may have broad antitumor activity.

The 14-day MTD of GSK1363089 in both XL880-001 (Intermittent 5&9 regimen) and XL880-002 (daily regimen) is similar, with 1200mg (240mg x 5) and 1120mg (80mg x 14) administered over 14 days leading to very similar AUC(0-336h) of 14910 and 15110ng\*hr/mL, respectively. Adding a cohort of subjects treated with the daily regimen will allow characterization of the safety, efficacy, and levels of exposure provided by two schedules of GSK1363089, as well as an exploration of whether the intermittent 5&9 regimen provides suboptimal exposure over time and whether continuous exposure provide better efficacy.

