## **2. STUDY OBJECTIVES**

The primary objectives of this study are as follows:

- To determine the confirmed response rate of GSK1363089 treatment in subjects with gastric carcinoma or adenocarcinoma of the gastroesophageal junction or of the distal esophagus.
- To further evaluate the safety and tolerability of GSK1363089.

The secondary objectives of this study are as follows:

- To assess the disease stabilization rate, progression-free survival, duration of stable disease, and overall survival in subjects with gastric carcinoma or adenocarcinoma of the gastroesophageal junction or of the distal esophagus who are treated with GSK1363089.
- To characterize the PK and pharmacodynamic parameters of GSK1363089 in subjects with gastric carcinoma or adenocarcinoma of the gastroesophageal junction or of the distal esophagus.

Note: Each of the primary and secondary study objectives will be assessed for each dosing Cohort (1 – Intermittent 5 days on/9 days off dosing; 2 – daily dosing) separately and together.

The exploratory objectives of this study are as follows:

- To characterize the *c-MET* amplification status of patients in this study population and possible associations with response to GSK1363089 therapy. In addition, the mutational status as well as expression of *c-MET* and related genes and proteins (e.g., RON) and of relevant downstream targets may also be assessed.
- To evaluate the efficacy and safety profiles between two GSK1363089 dosing regimens - Intermittent 5 days on/9 days off and daily.
- To evaluate the effect of GSK1363089 treatment on potential pharmacodynamic markers of clinical activity in paired tumor biopsies (e.g. phospho-MET).

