### **3. STUDY DESIGN**

#### **3.1. Overview of Study Design**

This is a Phase 2, non-randomized, sequential-cohort, open-label, single-stage, safety and efficacy study, with an initial cohort of subjects enrolled onto the Intermittent 5&9 regimen, and then a 2nd cohort of subjects enrolled onto the daily regimen. Enrolment into Cohort 2 will not begin until enrolment into Cohort 1 has completed.

The estimated length of the study is 40 months for subject accrual and treatment. This study consists of a Pre-Treatment Period (screening and baseline evaluations), a Study Treatment Period, an optional Treatment Extension Period, and a Post-Treatment Period (including an end-of-treatment visit and an extended follow-up period). Throughout the study, AEs will be recorded as volunteered. Adverse events will be graded according to the NCI CTCAE v3.0. A copy of this grading scale will be provided to the study sites upon request, or it can be accessed at <http://ctep.cancer.gov/reporting/ctc.html>. All doses of GSK1363089 are to be administered on an empty stomach.

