**8.1.1. Analysis Populations**

The safety population will be defined as all subjects who received at least one dose of study drug.

The evaluable population will include subjects in the safety population who:

1. have a baseline and post-baseline tumor assessment, and
2. who have received at least 75% of protocol-mandated doses during the 8-week study treatment period;

as well as subjects who, prior to completing the 8-week Study Treatment Period:

1. require study drug discontinuation due to GSK1363089-related toxicity, or
2. have objective evidence of progressive disease.

All efficacy analyses will be performed on both the safety and the evaluable populations.

All safety analyses will be performed on the safety population.

All efficacy and safety analyses will be conducted on each cohort separately as well as together.

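### The exploratory comparison of the two regimens mixes schedule with tumour type, because Cohort 2 has wider eligibility than Cohort 1 and no analysis of the shared population is pre-specified

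*Combined protocol and SAP*

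**What the plan says.** **Eligibility.** Section 3.3.1 sets entry to the intermittent cohort by tumour type: "poorly-differentiated, advanced or metastatic gastric carcinoma or adenocarcinoma of the gastroesophageal junction will be eligible for enrollment into Cohort 1". For Cohort 2 it adds the distal esophagus and says: "This will include subjects with well- and moderately-differentiated tumors, as well as poorly-differentiated tumors". Footnote 1 to the Synopsis (Number of Subjects) gives the history: "Prior to Amendment 3.0, only subjects with poorly-differentiated gastric carcinoma or adenocarcinoma of the gastroesophageal junction were included".

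**Order.** Section 3.1 describes a non-randomized design with sequential cohorts: "Enrolment into Cohort 2 will not begin until enrolment into Cohort 1 has completed".

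**Purpose.** One reason that Section 1.4.2 gives for adding the daily cohort is to explore "whether continuous exposure provide better efficacy". Section 2 lists as an exploratory objective: "To evaluate the efficacy and safety profiles between two GSK1363089 dosing regimens - Intermittent 5 days on/9 days off and daily".

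**Analysis.** Section 8.1.1 states: "All efficacy and safety analyses will be conducted on each cohort separately as well as together". The Synopsis (Statistical Methods) and the note in Section 2 also plan both views. Section 8.1.2 summarises ORR by cohort, and Section 8.2 sets the hypothesis and the rule of 6 responders in 30 for each cohort. Section 8.1.2 allows stratified or logistic models of response, but these are optional and depend on a sufficiently high response rate. The candidate variables include disease characteristics; grade, tumour site and cohort are not named. The only defined strata are by c-MET amplification (3.3.1, 8.2).

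**The concern.** Every Cohort 1 subject receives the intermittent schedule and has a poorly-differentiated gastric or GEJ tumour. Every Cohort 2 subject receives the daily schedule and may have any grade, or a distal esophageal tumour. Schedule is thus aligned with an eligibility change, and a crude difference between cohorts cannot be attributed to schedule. Nothing in the protocol acknowledges the difference in case mix or plans an analysis in the population that both cohorts share.

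The factor that changed could matter for this drug. Section 1.2 reports c-MET amplification in scirrhous and poorly-differentiated specimens, and Section 3.3.1 cites evidence that amplified gastric cell lines respond more to a c-MET inhibitor. At stake is the reading of the regimen contrast, which could inform the choice of schedule, and the meaning of a combined ORR.

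**Working it through.** **1. The plan's own figures.** Exact binomial tails with null rate 0.10 and alternative 0.25 (Section 8.2):

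- 6 of 30: P(X ≥ 6 | 0.10) = 0.0732 and P(X ≤ 5 | 0.25) = 0.2026. Both match.
- 8 of 40: 0.0419 and 0.18195, against 0.0419 and 0.18196 stated. They match apart from the last digit.

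These are properties of each cohort alone and do not depend on whether the cohorts are comparable.

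**2. Difference produced by case mix alone.** The documents give no ORR by grade or site and no expected Cohort 2 mix, so this step rests on assumptions: no schedule effect; the plan's own 0.10 and 0.25 as the rates in the two tumour groups, in either order; and a share w of Cohort 2 in the added types.

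Cohort 2 ORR = w × p(added) + (1 − w) × p(poorly-differentiated gastric/GEJ). For w = 0.50: 0.50 × 0.25 + 0.50 × 0.10 = 0.175, against 0.10 in Cohort 1.

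| p(poor) / p(added) | w | Cohort 2 ORR | Cohort 2 − Cohort 1 | P(≥6/30), Cohort 1 | P(≥6/30), Cohort 2 |
|---|---|---|---|---|---|
| 0.10 / 0.25 | 0.25 | 0.1375 | +3.75 points | 0.073 | 0.224 |
| 0.10 / 0.25 | 0.50 | 0.175 | +7.5 points | 0.073 | 0.432 |
| 0.10 / 0.25 | 0.75 | 0.2125 | +11.25 points | 0.073 | 0.637 |
| 0.25 / 0.10 | 0.25 | 0.2125 | −3.75 points | 0.797 | 0.637 |
| 0.25 / 0.10 | 0.50 | 0.175 | −7.5 points | 0.797 | 0.432 |
| 0.25 / 0.10 | 0.75 | 0.1375 | −11.25 points | 0.797 | 0.224 |

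If the two rates are equal, the difference is 0 for every w.

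**3. What the pooled ORR shows.** Results of 6/30 and 6/30, or of 2/30 and 10/30, both pool to 12/60 = 20%, exact 95% interval 10.8% to 32.3%. The second pair differs between cohorts (Fisher p = 0.021). The pooled figure describes the enrolled mix and says nothing about either regimen.

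**4. Power of an all-subject contrast.** For 0.10 versus 0.25 with 30 per cohort, power at two-sided 0.05 is 0.33 (normal approximation) or 0.21 (exact Fisher). About 100 per cohort would be needed for 80% (normal approximation).

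**5. Precision in the shared population.** Cohort 2 also admits poorly-differentiated gastric/GEJ subjects, so a restricted comparison is possible. With an assumed ORR of 0.175 in both cohorts and m such subjects in Cohort 2, the 95% half-width is 1.96 × √[0.175 × 0.825 × (1/30 + 1/m)]:

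- m = 30: 0.19
- m = 23: 0.21
- m = 15: 0.24
- m = 8: 0.30

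**The case against.** The strongest reply is that the plan claims little. The primary question is asked within each cohort, with its own rule and error rates. The regimen comparison is exploratory, in a study declared non-randomized and sequential, with no between-cohort test, margin or equivalence claim. Attribution to schedule would be unsafe even with identical eligibility, because of calendar time. All of this stands, and it limits the point to how the contrast and the pooled figure are read.

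Other parts of the reply also stand:

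- Section 1.2 itself describes the relation between c-MET overexpression and histologic subtype as less clear, and both cohorts are stratified on amplification. That partly covers the proposed mechanism.
- Disease characteristics could include grade and site, and Section 8.1 defers detail to a separate SAP whose text is not in the material supplied. The gap is therefore shown for this protocol only.
- A 7.5-point artefact is smaller than the standard error of a 30-versus-30 difference (9.8 points at ORR 0.175).
- A lower chance of reaching 6/30 where the enrolled population truly responds less is the within-cohort test working properly.

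The reply does not remove the gap. Optional models that depend on the response rate and leave grade and site unnamed are not a pre-specified analysis, and with about 6 responders per cohort they could adjust for little. Being exploratory is a reason to label the contrast; it does not make the contrast interpretable.

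**Conclusion.** The concern holds in a limited form. The exploratory regimen comparison is confounded with tumour type and calendar time. The pooled ORR is an average weighted by case mix and schedule, and it cannot be assigned to a regimen. On the assumed rates, case mix alone could produce a difference of 3.75 to 11.25 points in either direction, or none if ORR does not vary by grade or site. The documents do not fix the size or the sign.

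A reader might infer three stronger conclusions, which the documents do not support:

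- **That the study cannot meet its primary ORR objective.** The tests are within cohort and their error rates reproduce.
- **That the pooled ORR is itself confounded.** It is an average, not a contrast, and a valid description of the subjects enrolled.
- **That Cohort 1's ORR would be reported for tumour types it did not enrol, because Section 2 names all three sites.** Section 2 reads as a study-level statement, and the Synopsis footnote and Section 3.3.1 disclose the restriction. That is a matter of drafting.

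This is an inexpensive improvement to the analysis plan. It does not invalidate the design.

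**What to change.** 1. In Section 8.1.2, pre-specify a between-cohort efficacy comparison restricted to poorly-differentiated gastric/GEJ subjects, presented beside the all-subject comparison.
2. Report Cohort 2 ORR separately for that subset and for the added tumour types.
3. Record differentiation grade and tumour site for every subject, and add grade to the central pathology review in Section 5.9.4, which currently mentions only confirmation of the diagnosis.
4. Label the regimen contrast and the pooled ORR as descriptive.

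Dosing and enrolment do not change. The cost is protocol and SAP wording, plus grading at a review that is already planned. The subset should be fixed before results are seen, since one chosen afterwards would carry little weight.

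The restricted contrast is less precise: a half-width of about 0.24 with 15 such Cohort 2 subjects, against 0.19 for 30 versus 30, at the assumed ORR of 0.175. It also leaves two imbalances in place: calendar time, and the possible late addition to Cohort 2 of subjects pre-screened by FISH for c-MET amplification (3.3.1). Both should be stated wherever the comparison is reported.

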### 3.4. Dose Reduction or Treatment Delay for Toxicity

For the purpose of this protocol and for assistance with making decisions regarding dose reduction or delays, the following CTCAE Grade 3 definitions have been slightly modified (modifications are in italics):

- Grade 3 hypertension *despite optimal antihypertensive therapy with one or more drugs* (see [Management of Treatment-Emergent Hypertension](#) for information regarding management of treatment-emergent hypertension)
- Grade 3 nausea, vomiting, or diarrhea *despite prophylaxis and/or treatment* (see Section [4.4.2](#) for information regarding supportive care treatment)

In the event of treatment emergent hepatotoxicity, irrespective of whether the investigator considers it related to study drug, the management guidelines described in Section [4.4.4](#) should be followed.

If a subject experiences a new onset of unacceptable symptoms or signs of toxicity (excluding hepatotoxicity which is covered above), but in the investigator's opinion should continue to receive study drug, study treatment may be delayed for up to 21 days, then resumed either at the same dose or at a reduced dose, according to the criteria set out in Sections [3.4.1](#) and [3.4.2](#). The details of how to dose-reduce subjects are set out in Sections [3.4.3](#) and [3.4.4](#).

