#### 4.4.4. Management of Treatment-Emergent Hepatotoxicity

In the event of treatment-emergent hepatotoxicity, potential contributing factors such as concomitant medications, viral hepatitis, choledocholithiasis, and hepatic metastases should be investigated. Concomitant medications known to be hepatotoxic which may be contributing to liver dysfunction should be discontinued or replaced with alternative medications to allow for recovery of liver function. As generally understood, ALT  $>3$  x ULN and concomitant bilirubin  $\geq 2.0$  x ULN ( $>35\%$  direct bilirubin), in the absence of elevated alkaline phosphatase or biliary injury, suggests significant liver injury.

Table 3 shows the liver-enzyme entry criteria, split by whether there is liver involvement.

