**Table 3 Liver Enzyme Entry Criteria**

|                        | No liver involvement                                     | With liver involvement                               |
|------------------------|----------------------------------------------------------|------------------------------------------------------|
| ALT and AST     | $\leq 2.5 \times \text{ULN}$                             | $\leq 5 \times \text{ULN}$                           |
| Total bilirubin | $\leq 1.5 \text{ mg/dL}$ or $\leq 1.5 \times \text{ULN}$ | $\leq 2 \text{ mg/dL}$ or $\leq 2 \times \text{ULN}$ |

Liver chemistry stopping and follow-up criteria have been designed to ensure subject safety and evaluate liver event etiology. [Appendix G](#) provides a flow diagram of these criteria.

Therapy with GSK1363089 should be terminated if any of the following criteria are met:

11. ALT  $\geq 3 \times \text{ULN}$  or  $\geq 3 \times \text{Baseline}$  (if baseline ALT  $> \text{ULN}$ ) **and** bilirubin  $\geq 1.5 \times \text{ULN}$  or  $\geq 1.5 \times \text{Baseline}$  (if baseline bilirubin  $> \text{ULN}$  **and**  $> 35\%$  direct bilirubin)
12. ALT  $\geq 5 \times \text{ULN}$  or  $\geq 5 \times \text{Baseline}$  (if baseline ALT  $> \text{ULN}$ )
13. ALT  $\geq 3 \times \text{ULN}$  or  $\geq 3 \times \text{Baseline}$  (if baseline ALT  $> \text{ULN}$ ) if associated with the appearance or worsening of hepatitis symptoms
14. ALT  $\geq 3 \times \text{ULN}$  or  $\geq 3 \times \text{Baseline}$  (if baseline ALT  $> \text{ULN}$ ) that persists for  $\geq 4$  weeks

Baseline ALT and total bilirubin should be calculated as the average of **all** liver chemistry results obtained from Screening through Day 1. This requirement is based on the variability of baseline and screening ALT values observed in an earlier study.

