**When any of the liver chemistry stopping criteria is met, do the following:**

- **Immediately withdraw GSK1363089**
- Report the event to GSK within **24 hours** of learning its occurrence
- Complete the liver event CRF
- Complete the SAE data collection tool if the event also meets the criteria for an SAE
- Perform liver imaging (CT scan or MRI) within 7 days
- Complete the liver imaging and/or liver biopsy CRFs if these tests are performed
- Perform liver event follow-up assessments, and monitor the subject until liver chemistries resolve, stabilize, or return to baseline values as described below
- Withdraw the subject from the study after completion of the liver chemistry and viral studies and resolution of liver function to baseline levels
- Do not rechallenge with investigational product

In addition, for criterion 1:

- Make every reasonable attempt to have subjects return to clinic within **24 hours** for repeat liver chemistries, liver event follow-up assessments (see below), and close monitoring
- A specialist or hepatology consultation is recommended
- Monitor subjects twice weekly until liver chemistries (ALT, AST, alkaline phosphatase, bilirubin), complete blood count, platelet count, and prothrombin time resolve, stabilize or return to within baseline values
- Measure anti-nuclear antibody, anti-smooth muscle antibody, and Type 1 anti-liver-kidney microsomal antibodies
- Liver biopsy may be performed at the discretion of the investigator

For all other criteria:

- Make every reasonable attempt to have subjects return to clinic **within 24 to 72 hours** for repeat liver chemistries and liver event follow-up assessments (see below)
- Monitor subjects weekly until liver chemistries (ALT, AST, alkaline phosphatase, bilirubin) resolve, stabilize or return to within baseline values

Subjects with ALT  $\geq 3 \times \text{ULN}$  **but**  $< 5 \times \text{ULN}$  or  $\geq 3 \times \text{Baseline}$  (if baseline ALT  $> \text{ULN}$ ) **but**  $< 5 \times \text{Baseline}$  (if baseline ALT  $> \text{ULN}$ ) **and** bilirubin  $< 1.5 \times \text{ULN}$  or  $< 1.5 \times \text{Baseline}$  (if baseline bilirubin  $> \text{ULN}$ ), without hepatitis symptoms or rash, and who can be monitored weekly for 4 weeks:

- Can continue investigational product

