### **5.6.1. Liver Function Tests**

Liver function testing (LFT) will be performed at Screening/Baseline, at specific timepoints throughout the study and at the follow-up visit. LFT should include:

- Alanine aminotransferase (ALT)
- Aspartate aminotransferase (AST)
- Alkaline Phosphatase
- Total Bilirubin

A direct and indirect bilirubin level should be obtained if the total bilirubin level is  $\geq 1.5$  x ULN for subjects with normal liver function at baseline or  $\geq 1.5$  x baseline for subjects with abnormal liver function at baseline. Liver chemistry threshold stopping criteria and dose modification guidelines have been designed to assure subject safety. Guidelines for interpretation of the liver function tests are described in Section [4.4.4](#).

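### The liver stopping rule in 4.4.4 is ambiguous for subjects enrolled with raised ALT and, on its workable reading, can miss the injury pattern the section itself describes

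*Combined protocol and SAP*

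**What the plan says.** Section 3.4 directs treatment-emergent hepatotoxicity, whatever its cause, to 4.4.4. It then removes it from the rule that allows a delay of up to 21 days and a dose reduction: "excluding hepatotoxicity which is covered above".

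Section 4.4.4 contains four things that matter here.

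- **A described injury pattern.** ALT above 3x ULN with bilirubin at or above 2.0x ULN (more than 35% direct), "in the absence of elevated alkaline phosphatase or biliary injury, suggests significant liver injury". The limits are multiples of ULN and make no allowance for baseline.
- **Entry limits.** "Table 3 shows the liver-enzyme entry criteria, split by whether there is liver involvement": ALT and AST up to 2.5x ULN without liver involvement and up to 5x ULN with it.
- **Four stopping criteria.** "Therapy with GSK1363089 should be terminated if any of the following criteria are met". The first, third and fourth need ALT at 3x ULN, or 3x Baseline if baseline ALT is above ULN. They add, in turn, a bilirubin rise, hepatitis symptoms, and persistence for 4 weeks. The second needs ALT alone at 5x ULN, or 5x Baseline. Appendix G "provides a flow diagram of these criteria", with separate diagrams for normal and abnormal baselines.
- **A monitoring tier.** With ALT from 3x to below 5x (ULN, or Baseline if raised), bilirubin below 1.5x and no hepatitis symptoms or rash, subjects who can be monitored weekly "Can continue investigational product".

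Withdrawal of drug, the 24-hour liver-event report, liver imaging, the follow-up panel and the instruction "Do not rechallenge with investigational product" all begin only when a stopping criterion is met.

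**The concern.** The criteria join the two scales with *or*, and the protocol does not say whether the Baseline multiple is an alternative to the ULN multiple or a replacement for it. Each reading causes a problem for subjects who enter with raised ALT.

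If it is an alternative, subjects whom the protocol admits would be stopped for values they had at entry. If it is a replacement, the threshold rises in proportion to baseline, while the described injury pattern stays fixed in multiples of ULN. A subject can then match that pattern and meet no stopping criterion, and 3.4 has already withdrawn its delay-or-reduce rule for hepatotoxicity. The same values in a subject with normal baseline would require permanent discontinuation.

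At stake are the safety of those subjects and consistent handling across up to 20 sites.

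**Working it through.** **Inputs.** Entry limits of 2.5x and 5x ULN come from 4.2 (criterion 9) and Table 3. The stopping multiples of 3 and 5, the bilirubin multiple of 1.5 and the injury pattern come from 4.4.4. Write baseline ALT as b x ULN and all on-treatment values in multiples of ULN.

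**Literal reading (either multiple is enough).**
- For every b > 1, 3b > 3 and 5b > 5. Meeting the Baseline multiple therefore always implies meeting the ULN multiple, and the Baseline clauses have no effect.
- b = 5 with ALT unchanged at 5: 5 >= 5, so the second criterion is met on Day 1.
- b = 4 with ALT unchanged at 4: 4 >= 3, so the fourth criterion is met after 4 weeks.
- b = 4, ALT 13, normal bilirubin, no symptoms: 13 >= 5 means terminate. But 13/4 = 3.25, which lies between 3x and 5x Baseline and so falls in the monitoring tier, where drug may continue. The two instructions conflict.

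**Replacement reading (Baseline replaces ULN when b > 1).** The first, third and fourth criteria and the monitoring tier start at 3b; the second criterion starts at 5b.

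| Baseline ALT (x ULN) | 3b (x ULN) | 5b (x ULN) |
|---|---|---|
| normal | 3 | 5 |
| 1.5 | 4.5 | 7.5 |
| 2.5 (entry limit, no liver involvement) | 7.5 | 12.5 |
| 4 | 12 | 20 |
| 5 (entry limit, liver involvement) | 15 | 25 |

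Two examples, each with normal baseline bilirubin, mostly direct bilirubin on treatment, normal alkaline phosphatase and no biliary injury:

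- *No liver involvement.* b = 2.5, ALT 7, bilirubin 3. The pattern is present (7 > 3 and 3 >= 2.0). But 7/2.5 = 2.8, below 3, so no criterion is met, even with symptoms or 4 weeks' persistence.
- *Liver involvement.* b = 4, ALT 11, bilirubin 2.5. The pattern is present (11 > 3 and 2.5 >= 2.0). But 11/4 = 2.75, below 3, so again no criterion is met.

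With normal baseline, both sets of values meet the first criterion (ALT >= 3, bilirubin >= 1.5) and the second (ALT >= 5).

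**How many subjects.** The documents do not give the share with baseline ALT above ULN. Assuming 10% to 40% of 60 to 80 evaluable subjects, the number is 0.10 x 60 = 6 to 0.40 x 80 = 32. Section 5.11 reports related ALT increase in 11%. If that rate applied regardless of baseline, 0.11 x 6 = 0.7 to 0.11 x 32 = 3.5 subjects would have any such increase. Fewer would have the bilirubin pattern, possibly none.

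**The case against.** The strongest reply is that the printed *or* already stops both example subjects, so there is no gap. On the words alone that is true, but the reading fails for the reasons worked through above. Section 5.6.1 (direct bilirubin) and Appendix G also split their rules by normal and abnormal baseline, which supports replacement. If some sites did read it literally, they would apply a permanent stop differently from the others, and that too calls for a clarifying sentence.

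Second, baseline-relative limits look deliberate: 4.4.4 prescribes an averaged baseline because ALT varied in an earlier study. The injury pattern is offered as general understanding and is not itself a threshold. This stands as a reason to leave the isolated-ALT limits alone. It does not explain why the combined pattern should have no consequence at raised baseline.

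Third, other safeguards exist, and they are substantial. Section 4.4.4 calls for a work-up of contributing causes. Section 5.1 leaves adjustment or delay to the investigator, though it refers back to 3.4. Section 5.10 permits withdrawal and requires the investigator to confer with the sponsor on a serious or intolerable event. Section 7.2.1 requires SAE reports within 24 hours, 7.2.3 requires repeat tests, and Section 10 sets a monthly safety review. Together they make a sensible response likely. None of them requires a stop.

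Three stronger inferences should be resisted. A reader might conclude that subjects can reach 15x ULN with no response at all, but that figure is the extreme case and the safeguards above still apply. A reader might take the sentence in 5.6.1, "Liver chemistry threshold stopping criteria and dose modification guidelines have been designed to assure subject safety", as pointing to dose rules that were never written. The Appendix G diagrams are not visible in the copy reviewed, so that cannot be concluded. Nor do the documents show that raised ALT at entry means poor hepatic reserve; entry also caps bilirubin.

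**Conclusion.** The point holds in a limited form. As worded, the criteria either stop eligible subjects for unchanged values and conflict with the monitoring tier, or raise the first ALT stop to 7.5x ULN at baseline 2.5x and 12x at baseline 4x. In the second case the combined pattern can occur with no mandatory stop, liver-event report or rechallenge ban.

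The gap depends on the replacement reading, which is the only one that fits the rest of the protocol. It also assumes that the unseen Appendix G diagrams add no further branch; 4.4.4 describes them as showing the same criteria. The expected number of affected subjects is small and rests on an assumed share with raised baseline. The case for a change is that the consequence for an affected subject could be serious and the correction is short.

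**What to change.** 1. State in 4.4.4 that the Baseline multiple replaces the ULN multiple when the baseline value is above ULN.
2. Add one stopping criterion for subjects with baseline ALT above ULN. It requires all of the following:
   - ALT above 3x ULN and clearly above baseline, for example at least 1.5x Baseline, with the multiple to be confirmed by the sponsor's safety physicians.
   - Bilirubin at least 2.0x ULN, and at least 1.5x Baseline if baseline bilirubin is above ULN, with more than 35% direct.
   - No biliary injury and no new rise in alkaline phosphatase over the subject's own baseline. Using the subject's own baseline keeps in scope those who enter with raised alkaline phosphatase.
3. Check that the Appendix G diagrams agree.

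Leave the isolated-ALT thresholds and the 3.4 exclusion unchanged.

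With the 1.5x multiple, both example subjects would stop (7/2.5 = 2.8 and 11/4 = 2.75, each at least 1.5). A subject steady at 4x ULN would not (4/4 = 1.0).

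The cost is a few sentences and a check of two diagrams. No routine tests are added: 5.6 already includes ALT, alkaline phosphatase and total bilirubin, and 5.6.1 already requires direct bilirubin once total bilirubin reaches 1.5x ULN or 1.5x baseline. The downside is that a few subjects whose tests rise because of liver metastases may stop earlier. The existing criteria already carry that risk, since they apply whatever the cause.
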